## Abstract

**Background:**

Studies on walking football have found positive effects on health; however, there are still several research gaps when applying walking football programs for patients with type 2 diabetes.

**Objective:**

This study aims to test the effectiveness of a walking football exercise program on glycemic control and cardiovascular risk factors in middle-aged and older men with type 2 diabetes.

**Methods:**

The study will be run as a randomized controlled trial with a 6-month duration in Portugal. Eligible participants will be randomized using a 1:1 ratio for intervention or control groups and compared using an intention-to-treat analysis. The intervention will consist of a walking football exercise program. The control group will continue with usual care in primary health care units. The primary outcome will be the mean difference in glycated hemoglobin between intervention and control groups after 6 months. Secondary outcomes include the mean differences in fasting blood glucose, total cholesterol, low-density lipoprotein cholesterol, high-density lipoprotein cholesterol, triglycerides, systolic and diastolic blood pressure, body mass index, waist circumference, fat-free mass, and fat mass. Additionally, secondary outcomes include the incidence of exercise-related injuries and adverse events and the walking football exercise program’s cost-utility.

**Results:**

The study protocol is being prepared to be submitted to the Health Ethics Committee of the Northern Regional Health Administration, Portugal. After approval, participant recruitment will start in primary health care units in Porto's metropolitan area by family medicine doctors.

**Conclusions:**

Walking football might have the potential to be effective in improving glycemic control and cardiovascular risk factors, with a low rate of exercise-related injuries and adverse events and a good cost-utility ratio. Therefore, walking football may be a sustainable intervention strategy for type 2 diabetes management.

**International Registered Report Identifier (IRRID):**

PRR1-10.2196/28554

## Introduction

### Background and Rationale

Type 2 diabetes (T2D) is a global public health concern considering its morbidity, mortality, and health expenditure [1]. In 2019, it was estimated that 463 million adults (20-79 years old) worldwide were diagnosed with diabetes, corresponding to 9.0% of all adults in this age group [1] and representing nearly 90% of T2D cases. Increased exposure to environmental factors, such as obesity and physical inactivity, has been associated with the alarming increase in the prevalence of diabetes [1]. Portugal is one of the European countries with the highest prevalence of diabetes. In 2015, the prevalence of diabetes in the adult population (25-74 years old) was 9.9% [2]. The prevalence was higher in men than in women (12.1% vs 7.8%), and higher in individuals aged 65-74 years (23.8%) compared with younger individuals [2].

The benefits of physical activity in the prevention and control of T2D have long been documented [3-6]; however, a considerable proportion of individuals with T2D do not adhere to the recommendations proposed by international organizations (eg, American Diabetes Association, American College of Sports Medicine) [7,8]. Data from Portugal revealed that about 60% of individuals with T2D reported not practicing any type of exercise [9], demanding interventions to increase physical activity levels in this population.

Recreational football is conducted as small-sided games, from 3 vs 3 to 7 vs 7, practiced 2-3 times per week, in sessions of 45-60 minutes. The practice of recreational football is an intermittent activity, with participants moving at slow speed, but with consecutive changes in direction, accelerations, and decelerations, leading to periods of moderate-to-vigorous intensity. This intermittent activity has shown cardiovascular, metabolic, and neuromuscular benefits across different populations [10-14]. This can contribute to increased physical activity levels and, therefore, to the control of several noncommunicable diseases, including T2D [10-14].

Exercise-related injuries and the high exercise intensities observed in recreational football led some football clubs to develop walking football strategies for their older players [15]. Walking football follows football’s general rules, but it does not allow players to run or have physical contact, and the ball must always be played below the players’ average waist height [16]. Available studies on walking football have reported engagement and satisfaction with the modality, the pattern of exercise intensity (from light to vigorous), and health benefits (namely on body composition, aerobic fitness, blood pressure, cognitive function, psychologic well-being, and quality of life) [17-22].

Only 3 studies provided details regarding the participants’ medical conditions [17,20,22]. Participants were mainly middle-aged and older men with overweight, obesity, hypertension, or T2D. Characterization of medical conditions and cardiovascular risk factors seems particularly important when extrapolating exercise effects for some populations. Patients with T2D have an increased risk of injuries and acute adverse events associated with exercise training compared with healthy subjects [23]. Indeed, efforts for safety are fundamental in exercise programs and may compromise participants’ adherence.

A 12-week study that tested the feasibility and safety of a walking football program in middle-aged and older men with T2D in a quasiexperimental design found that the most common adverse events were falls and musculoskeletal injuries, and no acute metabolic or hemodynamic adverse events were observed. No registered injuries or adverse events were reported, mainly due to the safety protocols applied before, during, and after each exercise session [22].

Studies on walking football showed positive effects on health. However, there are still several research gaps regarding walking football in patients with T2D. It includes limitations in study designs, sample sizes, length of the programs, assessment of variables that may influence adherence to the programs (such as the enjoyment), and impact on glycemic control and cardiovascular risk factors.

### Objectives

This study aims to test the effectiveness of a 6-month walking football exercise program on glycemic control and cardiovascular risk factors in middle-aged and older men with T2D.

This study will be accomplished through the following specific objectives: (1) evaluate the effects of a walking football exercise program on glycemic control, blood lipid profile, blood pressure, anthropometric profile, and body composition; (2) assess exercise-related injuries and adverse events of a walking football exercise program; (3) assess the cost-utility of a walking football exercise program.

## Methods

This protocol follows the Standard Protocol Items: Recommendations for Interventional Trials (SPIRIT) statement [24]. The SPIRIT checklist is available in Multimedia Appendix 1, and the trial for this protocol will be registered at ClinicalTrials.gov.

### Design

This study is based on a parallel-group, randomized controlled trial with a 6-month duration. Eligible participants will be randomized using a 1:1 ratio within each primary health care unit (PHCU) to intervention or control groups. The intervention will consist of a 60-minute walking football exercise program, 3 times per week (nonconsecutive days), for 24 weeks. The control group will maintain daily life routines and continue with usual care. The study design is represented in Figure 1.

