### Participants

Participants will be recruited from 5 PHCUs. Family medicine doctors at these PHCUs will extract a list of potential participants from the information system and contact them by telephone. Each PHCU is expected to enroll 40 patients, corresponding to a total of 200 participants.

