### Data Analysis and Sample Size

The number of participants to be involved was defined to test the superiority of walking football compared with usual care, using intention-to-treat analysis. For a 1:1 ratio of the intervention and control groups, significance level of 5%, and statistical power of 80%, a total of 162 participants will be needed to detect a mean difference of at least 0.35% in the primary outcome (glycated hemoglobin), based on previous meta-analyses [33,34]. Assuming the complete follow-up of at least 80% of the participants, a total of 200 participants will be enrolled.

We will use a 2-way (group*time) analysis of variance with repeated measures to compare the mean differences between intervention and control groups.

For the cost-utility analysis, we will calculate the walking football implementation costs compared with the usual care. Costs include technical training for the professionals involved, patients’ medical assessments, material for capillary blood glucose and blood pressure evaluations, football equipment, sports facility rental, sports insurance, and payment to nurses and football coaches. The costs of the intervention and reported gains in quality of life (based on quality-adjusted life years) [27] will be used to calculate the incremental cost-utility ratio (ICUR). ICUR will be compared with the World Health Organization thresholds for health interventions based on per capita gross domestic product.

The amount of missing data is expected to be low considering the training of all the staff and the use of standardized procedures for data collection. No imputation is being planned.

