### Limitations

Some limitations need to be addressed: First, the lack of participant, health care professional, and elements of the research team’s blinding may introduce bias that may affect the outcome assessment. Nevertheless, our primary outcome is an objective measure — glycated hemoglobin, measured by blood clinical analysis — which may reduce the impact on the lack of blinding.

Second, contamination may occur since randomization units are individuals and not PHCUs, and there is proximity in the geographical area for participants from each PHCU. However, education of all research members and participants towards contamination and clear information about the purposes of the trial may minimize its occurrence.

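### Randomisation is 1:1 within five health care units, but the stated group-by-time ANOVA has no unit term: a small, conservative mismatch that costs almost nothing to remove

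*Protocol article*

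**What the plan says.** Allocation (Design): "Eligible participants will be randomized using a 1:1 ratio within each primary health care unit (PHCU) to intervention or control groups".

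Strata (Participants): "Participants will be recruited from 5 PHCUs", and "Each PHCU is expected to enroll 40 patients, corresponding to a total of 200 participants". That is about 20 men per arm in each unit.

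Unit of randomisation (Limitations): "contamination may occur since randomization units are individuals and not PHCUs". PHCU is therefore a stratum and not a cluster.

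Analysis (Data Analysis and Sample Size): "We will use a 2-way (group*time) analysis of variance with repeated measures to compare the mean differences between intervention and control groups". No other between-group model is given. PHCU, centre or stratum is not mentioned in connection with the analysis, and PHCU is not among the control variables listed under Data Collection.

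Timing (Data Collection, Table 1): HbA1c and the continuous secondary outcomes are assessed at baseline and at the end of the study, which gives two time points.

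**The concern.** When arms are balanced within a stratum, stratum differences drop out of the treatment contrast. The actual sampling variance of that contrast is then the within-stratum variance. A model without the stratum still counts between-stratum variation in its residual, so its standard error is larger than the design warrants. The interval is too wide, the test is conservative, and the precision that stratifying was meant to buy is not collected.

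The article leaves little room on power: 200 × 0.80 = 160 evaluable men, against 162 required. Even a small avoidable loss is worth recovering if recovering it is nearly free.

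**Working it through.** **1. What the stated test compares.** With two time points, the group-by-time F test is the square of the two-sample t test on each man's change from baseline to 6 months. A PHCU effect that is the same at both times is subtracted out within each man. What remains is p, the share of the variance in *change* that lies between PHCUs. The article gives no value for p, so it is varied here, with zero included.

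**2. The article's own sample size.** Inputs: difference 0.35, 5% significance (taken as two-sided; the article does not say), 80% power, 1:1, N = 162. No SD is stated. Solving for it with 81 per arm:

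SD = 0.35 × √(81/2) / (1.960 + 0.842) = 0.795.

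So 162 cannot be reproduced independently, but it follows if the SD is about 0.795. The allowance for loss is 162/0.80 = 202.5, so 203, against the stated 200. For the 160 men then expected (80 per arm), an SD of 0.79 gives 80.0% power. Both SDs are back-solved assumptions.

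**3. Effect of leaving PHCU out, by formula.** Let the model's standard error be SE = 0.79 × √(2/80) = 0.1249. With balance within PHCU, the true standard error is SE × √(1−p).

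- Excess interval width: 1/√(1−p) − 1
- Type I error: 2 × [1 − Φ(1.96/√(1−p))]
- Power without PHCU: Φ[(0.35 − 1.96 × SE)/(SE × √(1−p))]
- Power with PHCU: Φ[0.35/(SE × √(1−p)) − 1.96]

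| Share p of change variance (assumed) | Interval too wide by | Type I error without PHCU | Power without PHCU | Power with PHCU | Points lost |
|---|---|---|---|---|---|
| 0% | 0% | 5.0% | 80.0% | 80.0% | 0 |
| 5% | 2.6% | 4.4% | 80.6% | 82.0% | 1.4 |
| 10% | 5.4% | 3.9% | 81.3% | 84.0% | 2.7 |

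**4. Check by simulation.** Change scores were simulated for 5 PHCUs with 16 evaluable men per arm in each, total SD 0.795 and 20,000 replicates.

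| Share p | Type I error without / with PHCU | Power without / with PHCU |
|---|---|---|
| 0% | 0.051 / 0.051 | 0.794 / 0.794 |
| 5% | 0.047 / 0.053 | 0.794 / 0.806 |
| 10% | 0.040 / 0.049 | 0.806 / 0.830 |
| 20% | 0.033 / 0.049 | 0.830 / 0.873 |

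The losses are about 1.2 points at 5% and 2.4 points at 10%, slightly below the formula. The main reason is that the simulation draws the five PHCU effects at random. On average only about 4/5 of the between-PHCU variance then appears in the unadjusted residual, so the excess width is √[(1 − 0.2p)/(1 − p)] − 1, which is 2.1% at p = 5% and 4.3% at p = 10%. The two methods agree in direction and order of size, which is why the power loss is given as 1 to 1.5 and 2.5 to 3 points, rounded.

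**The case against.** **The change-score argument.** Differences between units in prescribing or case mix are mostly differences in HbA1c level, and the stated test already removes those. A reader might infer that all between-unit HbA1c variation stays in the error term; that does not follow from the model named. What matters is variation in change. The article asks both arms to keep their routines and usual care, and all units lie in one metropolitan area, so a share near zero is possible. This objection stands, and it is why the range starts at no loss. It does not show that the share is zero, since each unit's own team delivers usual care over the 6 months.

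**Balance is inferred.** The Assignment of Interventions section mentions a random number generator and no blocks. Under simple randomisation within units the unadjusted test would keep its nominal unconditional type I error. A 1:1 ratio within each unit, 40 men per unit and five exercise groups of 20 make enforced balance the natural reading, but the conservatism depends on it. If balance is only approximate, a PHCU term still gains precision and corrects chance imbalance.

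**A condensed article.** The article says that activity, diet, quality of life and medication will serve as control variables, yet its model sentence lists none of them, so that sentence may be a summary. This has some force. But the article is not silent on the model: "We will use a 2-way (group*time) analysis of variance with repeated measures" counts the factors and names both, and a fuller plan that added PHCU would depart from it.

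**False positives.** A reader used to cluster trials might infer that ignoring PHCU inflates type I error. The documents do not support that. Individuals are randomised within units, so the error runs the other way.

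**Conclusion.** The point holds, at modest size. The article randomises within PHCU and states a model that leaves PHCU out. If allocation is balanced within units, the cost ranges from nothing, when PHCU explains none of the variance in 6-month change, to an interval about 5.4% too wide and 2.5 to 3 points of power when it explains 10%. Those figures rest on two assumptions that the article does not supply: the PHCU share of change variance, and an SD of about 0.79.

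The treatment estimate is unbiased, and type I error stays at or below 5%. Power without the PHCU term remains at about 80% across that range, so nothing here shows the trial to be underpowered or its planned conclusion unsafe. This is an inexpensive gain in efficiency and coherence, not a threat to validity.

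**What to change.** In Data Analysis and Sample Size, state that the randomisation stratum is included in the primary HbA1c model and in the models for the continuous secondary outcomes. Two forms would do this:

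- Keep the repeated-measures ANOVA and add PHCU and PHCU-by-time. A PHCU main effect alone is not enough, because it does not adjust the group-by-time contrast.
- Model the change from baseline with group and PHCU as fixed effects. With two time points this is the same analysis. A model of the 6-month value adjusted for baseline, with PHCU as a fixed effect, would also carry the stratum, but baseline adjustment is a separate choice that this point does not require.

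The cost is 4 degrees of freedom (158 to 154 residual in the change-score model with 160 men) and a line of text. The PHCU of every participant is already known, and the sample size does not rise. The change should be made before outcome data are seen, so that it is not a post hoc change to the primary model.

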**Figure 1 figure1:**
[figure not shown]
Flow diagram of the randomized controlled trial.

### Setting

The study will be conducted in PHCU of Porto's metropolitan area, in the northern region of Portugal. A PHCU consists of multiprofessional teams, with a mean of 7 family medicine doctors, an equal number of family nurses, and administrative professionals. Family medicine doctors have a patient list that ranges from 1500 to 2000 patients, handling preventive activities and most of the acute and chronic health problems of the individuals. In these units, patients with chronic conditions, such as T2D, have regular consultations and close contact with their family medicine doctor.

### Participants

Participants will be recruited from 5 PHCUs. Family medicine doctors at these PHCUs will extract a list of potential participants from the information system and contact them by telephone. Each PHCU is expected to enroll 40 patients, corresponding to a total of 200 participants.

#### Inclusion Criteria

The participants will be selected according to the following criteria: diagnosis of T2D for at least 12 months; male; aged 55-70 years; glycated hemoglobin between 6.0% and 10.0%; not having started insulin therapy in the previous 6 months and/or sulfonylureas therapy in the previous 3 months; major complications of diabetes screened and controlled (diabetic retinopathy, diabetic nephropathy, and diabetic foot); no cardiovascular, respiratory, nor musculoskeletal contraindications to exercise; without symptoms of coronary artery disease; without limitations in gait or balance; nonsmokers at least for 6 months; not practicing supervised exercise for at least 6 months; independent living in the community; and availability for the exercise session schedule. Participants who fulfil the inclusion criteria will be invited to participate in the study and perform a treadmill cardiac stress test.

#### Exclusion Criteria

Individuals with issues identified in the cardiac stress test, namely asymptomatic cardiac or hemodynamic problems, will be excluded from the study.

### Intervention and Control Groups

Participants assigned to the intervention group will enroll in a walking football exercise program and receive basic sports material (eg, sports bag, t-shirt, and sports shoes). The participants will be organized into 5 groups of 20 players in different time schedules. Each group will have 60-minute walking football exercise sessions, 3 times per week (nonconsecutive days), for 24 weeks (72 sessions).

Walking football sessions will be conducted on a football field and supervised by a football coach certified by the Union of European Football Associations and by a nurse.

The sessions will consist of strength and conditioning exercises, technical skill drills, and small-sided and conditioned walking football games, including warm-up and cool-down periods.

The participants from the intervention and control groups will be asked to maintain daily life routines (lifestyle-related physical activity and dietary pattern) and continue with usual care (diabetes consultations and pharmacological regimen). In Portugal, the usual care at a PHCU already includes brief counseling for physical activity and sedentary behavior [25].

Participants from the control group will also receive basic sports material (eg, sports bag, t-shirt, and sports shoes).

All activities, participation rules, project team members, and the sports facilities will be presented to participants and their families before starting the intervention.

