**Exercise intensity**		
	Subjective	OMNI perceived exertion scale [28]
	Objective	Heart rate and time-motion tracking
Exercise sessions enjoyment		Physical Activity Enjoyment Scale [29]
Exercise-related injuries and adverse events		Observational/clinical/self-reported

All personnel involved in the study — nurses, nutritionists, medical doctors, football coaches, and sports scientists — will receive training before baseline assessments. This aims to standardize procedures.

Specifically, the principal investigator will provide training to the other research team members regarding the clinical assessments and forms.

The Portugal Football School of the Portuguese Football Federation will provide training to football coaches to ensure the walking football program is administered in a similar way in the different centers and according to a predefined manual.

A sports scientist will monitor, in real time, internal (heart rate [HR]) and external (eg, distance covered, number of actions) workload and apply the OMNI perceived exertion scale in all sessions.

The nurse must have training in emergency procedures, be responsible for measurements at exercise sessions, manage and record exercise-related injuries and adverse events, follow-up with participants, and refer to health care facilities if necessary.

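### The intervention is delivered in 5 exercise groups, but the stated power and the planned ANOVA make no allowance for team-specific variation in HbA1c change, so the stated 5% and 80% hold only if there is none

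*Protocol article*

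**What the plan says.** **Randomisation.** The Design section of the protocol article allocates men individually, 1:1, within each primary health care unit (PHCU). The Participants section expects 5 PHCUs with 40 men each.

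**Delivery.** Under Intervention and Control Groups, the intervention arm is split: "The participants will be organized into 5 groups of 20 players in different time schedules". Each group has three 60-minute sessions a week for 24 weeks (72 sessions), supervised by a coach and a nurse and including small-sided games. Controls continue with usual care and have no group sessions.

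**Standardisation.** The text after Table 2 (Data Collection) plans coach training and a predefined manual "to ensure the walking football program is administered in a similar way in the different centers".

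**Sample size and analysis.** Data Analysis and Sample Size gives a 1:1 ratio, 5% significance and 80% power, and concludes that "a total of 162 participants will be needed to detect a mean difference of at least 0.35% in the primary outcome". Enrolment is 200, assuming at least 80% complete follow-up. No SD, ICC or design effect is given. The analysis is a two-way (group by time) repeated-measures ANOVA, with no term for team or PHCU. The Limitations section covers blinding and contamination, not clustering by team.

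**The concern.** Men in one team share a time slot and play with one another for 72 sessions. Their HbA1c changes may therefore resemble each other more than those of men in different teams. Controls have no such grouping, so any such correlation arises in one arm only.

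An analysis that treats all men as independent gives the intervention mean more precision than it has when a team-specific component exists. The error then favours the intervention: the standard error is too small, the p-value too low and the interval too narrow. The stated 80% power also refers to a test that does not hold its 5% level. This matters for an unblinded superiority trial whose Discussion looks ahead to scaling the programme up.

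Both the power figure and the model are stated in the protocol, so the point concerns what is written and not a detail left to an analysis plan.

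**Working it through.** **Inputs from the protocol:** difference 0.35 percentage points; significance level 5% (two-sided assumed, since sidedness is not stated); power 80%; 162 evaluable, or 81 per arm; 200 enrolled; 5 intervention groups of 20.

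**Assumed:** the SD (back-solved below) and the team-specific ICC (0, 0.01, 0.02, 0.05).

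**Step 1: the plan's own figure.** No SD is stated, so 162 cannot be reproduced independently. Solve n per arm = 2(1.960 + 0.842)²·SD²/0.35² = 81 for the SD. This gives 0.795 by the normal approximation; solving with the t distribution gives 0.790. The figure is thus compatible with an ordinary two-sample comparison of independent men, but does not prove one. With a design effect of 1.30 in the intervention arm, an SD of 0.74 also gives 162.

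**Step 2: completers.** 200 × 0.80 = 160, so 80 per arm and 80/5 = 16 per team. With SD 0.79 and no clustering, SE = 0.79·√(2/80) = 0.1249 and power = Φ(0.35/0.1249 − 1.960) = 80%.

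**Step 3: clustering in one arm.** The design effect in the intervention arm is DE = 1 + (16 − 1)·ICC. The true SE is 0.79·√(DE/80 + 1/80), while the independence analysis targets 0.1249.

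- Type I error of the planned test = 2·[1 − Φ(1.960 × 0.1249/true SE)]
- Large-sample power of a test that allows for teams = Φ(0.35/true SE − 1.960)

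**Step 4: degrees of freedom.** With 5 teams, the Satterthwaite df are (v1 + v0)²/(v1²/4 + v0²/79), where v1 = 0.79²·DE/80 and v0 = 0.79²/80. Power then comes from the noncentral t distribution.

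| Team-specific ICC | DE | True SE | Type I error, planned test | Power, large-sample | df | Power, small-sample df |
|---|---|---|---|---|---|---|
| 0 | 1.00 | 0.1249 | 5.0% | 80% | 15.2 | 75% |
| 0.01 | 1.15 | 0.1295 | 5.9% | 77% | 13.5 | 71% |
| 0.02 | 1.30 | 0.1340 | 6.8% | 74% | 12.2 | 67% |
| 0.05 | 1.75 | 0.1465 | 9.5% | 67% | 9.7 | 58% |

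With SD 0.795 the power figures are at most about one point lower, and the type I error is unchanged because the SD cancels.

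**Step 5: simulation.** With 20,000 trials per setting (5 teams of 16, 80 controls), the independence test rejected under no effect in 5.1%, 5.7%, 6.6% and 9.1% of trials at the four ICCs. This agrees with the formula.

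**Step 6: correlation shared with controls.** Suppose teams coincide with PHCUs. With 5% of the variance shared by both arms of a PHCU and 1% specific to the team, the within-team ICC is 0.06. The simulated type I error of the independence test is nevertheless only 5.5%. The harm comes from the team-specific part alone.

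**The case against.** Several points on the other side are sound.

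- **Not every within-team correlation does harm.** A reader might infer that any positive correlation within teams makes the planned standard error too small. The documents do not support that. Randomisation is within PHCU, and 5 PHCUs of 40 men give 20 intervention men each, which matches 5 groups of 20. If teams coincide with PHCUs (plausible, but not stated), correlation shared with controls of the same PHCU cancels from the comparison, as step 6 shows.
- **162 does not prove that clustering was ignored.** A reader might infer this because an SD of about 0.79 fits the plain formula, but that SD was solved to fit. With no SD in the protocol, an unreported allowance cannot be excluded. What can be said is that none is stated.
- **Clustering alone does not take power from 80% to between 58% and 71%.** Those figures include the price of small-sample df with 5 teams, which already lowers power to 75% at an ICC of 0. At an ICC of 0.01, clustering itself costs about 3 points.
- **The ICC may be low.** Coach training and a common manual are there to limit differences in delivery. The protocol does not say that each team has its own coach or nurse.
- **Retention may exceed 80%.** If all 200 men are followed, large-sample power at an ICC of 0.02 is still about 82%. The type I error is then 7.2%, so better retention protects power but does not repair the test.
- **Model details often belong in an analysis plan, and 5 teams estimate a variance poorly.** Both are true, but the protocol has already named a model without a team term and claimed 80% power.

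These points limit the size and the wording. They do not remove the mismatch between group delivery in one arm and an analysis that assumes independence.

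**Conclusion.** The point holds in conditional form. The stated 5% and 80% are right for this design only if HbA1c change has no team-specific component. Should there be one, the planned test is too liberal: type I error 5.9% to 9.5% for an ICC of 0.01 to 0.05, against 5.0% at zero. A test that allows for teams has large-sample power of 77% to 67%, before the separate cost of few degrees of freedom.

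The size rests on an ICC that the documents do not give, a back-solved SD of 0.79, 80% follow-up in both arms and equal teams of 16. At the low end of the range the effect is small. The correction is cheap and the error would favour the intervention, so it should be made.

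**What to change.** 1. Record each man's exercise group from the start.
2. Analyse 6-month HbA1c with terms for group, baseline HbA1c and PHCU, plus a random team effect in the intervention arm only (each control as his own unit). Use Satterthwaite or Kenward-Roger degrees of freedom and report the estimated ICC.
3. Restate power along these lines: *80% assuming no clustering by exercise group; about 77%, 74% and 67% for a team-specific ICC of 0.01, 0.02 and 0.05 (large-sample).*
4. Note separately that the small-sample df from 5 teams cost further power: about 75% at an ICC of 0, and 71%, 67% and 58% at the three ICCs above, before any gain from baseline adjustment.
5. State the SD behind 162, and whether that number contains any allowance for clustering.

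**Cost:** changed wording and one extra recorded variable; a wider interval and a less favourable stated power; and a team variance that 5 teams estimate poorly. No change in enrolment or in delivery of the programme is needed.
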